**2.6 Efficacy Evaluation Criteria**

The primary indicator of treatment efficacy will be the change in LARS score from baseline.

**2.7 Adverse Events**

Any adverse reactions occurring during acupuncture treatment will be documented, including but not limited to bleeding, subcutaneous hematoma, numbness, and post-needling sensations such as soreness or distension. In cases of needle fainting (vasovagal response), acupuncture should be discontinued immediately, all needles withdrawn, and the patient placed in a supine position with warmth provided.

Minor subcutaneous bleeding resulting in small ecchymosis typically requires no intervention and will resolve spontaneously. If the affected area shows significant swelling, pain, or a large ecchymotic patch, cold compresses will be applied to reduce bleeding. For mild soreness or distension after treatment, local manual massage is recommended to relieve symptoms. In more severe cases, additional therapies may be used under medical supervision.

All adverse events will be managed symptomatically. If the acupuncturist is unable to resolve the issue, consultation with an appropriate medical specialist will be arranged. Any costs arising from adverse events related to the study intervention will be handled in accordance with applicable laws and regulations.

Assessment time point: Throughout the treatment period.

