2.1.5 Criteria for Withdrawal (Dropout)

① Participants who have signed informed consent, passed eligibility screening, and entered the randomized trial but subsequently discontinue the intervention or fail to complete the observation period as outlined in the protocol will be classified as dropout cases;

② In the event of a participant’s withdrawal, investigators should make every effort to contact the individual, document the reasons for withdrawal, and complete as many assessments as possible. All relevant trial records for dropout participants must be properly retained for archiving and for inclusion in full analysis set (FAS) statistical processing. Participants who withdraw will not be replaced.

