2.1.6 Suspension criteria

A participant will be withdrawn from the study under any of the following conditions:

① The occurrence of serious adverse events (SAEs), severe complications, or the need for reoperation, where the investigator determines that continued participation is not in the patient’s best interest;

② The development of other medical conditions that interfere with study assessments or make completion of acupuncture treatment infeasible, as judged by the investigator; such participants will be considered treatment failures;

③ Significant protocol deviations during trial implementation that compromise the evaluation of acupuncture efficacy;

④ The participant voluntarily requests to withdraw from the clinical trial during the study period by notifying the attending physician.

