**Table 2. Location of acupoints in SA group.**

| **Acupoints** | **Locations** |
| --- | --- |
| non-acupoint 1 | In the sacral region, 1 cun^a^ lateral to the Zhongliao (BL33) point |
| non-acupoint 2 | In the sacral region, 1 cun lateral to the Ciliao (BL32) point |
| non-acupoint 3 | On the lower limb, 2 cun above the medial malleolus, the medial side of the tibia is median, between the Liver and Spleen meridians |
| non-acupoint 4 | On the lower limb, at the midpoint of the line connecting Qiuxu (GB40) and Jiexi (ST41) points |
| non-acupoint 5 | On the abdomen, 2 cun below the umbilicus and 1 cun apart from the midline |
| non-acupoint 6 | On the abdomen, 2 cun above the anterior superior iliac spine |
| non-acupoint 7 | On the lower limb, on the lateral side of the lower leg, 3 cun below the Yanglingquan (GB34) point, between the Gallbladder and Bladder meridians |
| non-acupoint 8 | On the lower limb, on the medial side of the lower leg, 1 cun lateral to the Chengjin (BL56) point, between the Bladder and Stomach meridians |

^a^1 cun (≈20 mm) is defined as the width of the interphalangeal joint of patient’s thumb

Participants in both groups will receive acupuncture three times per week during the first four weeks (Weeks 1–4), and twice per week during the subsequent four weeks (Weeks 5–8), for a total of 20 sessions over an 8-week treatment period. No additional therapies targeting low anterior resection syndrome (LARS) will be permitted during the study period.

In cases of severe fecal incontinence, participants may be allowed to take loperamide hydrochloride capsules (Imodium) as needed for symptom relief.

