**Secondary outcome**

① Changes in LARS Score from Baseline at Week 2, 4, 6, 12 and 24.

② Proportion of Patients with Improvement in Bowel Dysfunction

At weeks 2, 4, 6, 8, 12, and 24, the number of patients improving from severe LARS to mild LARS, from mild LARS to no LARS and from severe LARS to no LARS will be determined according to LARS score.

③ Subjective distress of intestinal symptoms

We will assess subjective distress of intestinal symptoms by the Numerical Rating Scale (NRS) at Week 4, 8, 12 and 24, where 0 indicates no distress, and 10 represents the worst imaginable distress.

④ EORTC-QLQ-C30 Quality of Life Questionnaire

The core quality of life questionnaire developed by the European Organization for Research and Treatment of Cancer (EORTC-QLQ-C30), comprising 30 items. It includes 5 functions, 3 symptoms, 1 global health status, and 6 single-item measures. Higher scores on the functional scales indicate better quality of life, whereas higher scores on the symptom scales indicate worse quality of life. Patients were evaluated at weeks 4, 8, 12, and 24.

⑤ Bristol Stool Diary

During the week 0, 4, 8, 12 and 24, we will record bowel movement frequency, stool consistency and urgency over the past week.

⑥ Fecal Incontinence Quality of Life Scale (FIQL)

We will evaluate the quality of life in patients with fecal incontinence, covering four aspects: lifestyle changes, coping/behavior limitations, depression/self-perception, and social embarrassment at week 0, 4, 8, 12 and 24.

⑦ Diarrhea Wexner Score:

we will evaluate at week 0, 4, 8, 12 and 24.

⑧ Credibility and Expectancy Assessment:

The credibility of the intervention and participants’ treatment expectations will be evaluated immediately following the first treatment session.

⑨ Blinding Assessment:

Blinding effectiveness will also be assessed at the end of the first treatment session.

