**2.10 Quality Control**

① Participant recruitment will strictly follow the predefined diagnostic, inclusion, and exclusion criteria to ensure appropriate subject selection.

② Robust measures will be implemented to maintain allocation concealment. Randomization numbers will be managed by an independent randomization coordinator not involved in the trial. A randomization number will be issued only after the subject’s eligibility has been confirmed and the relevant information has been properly documented. This process ensures allocation concealment and prevents premature disclosure or manipulation of random sequences.

③ Standard Operating Procedures (SOPs) will be developed for all stages of the trial following expert consultation. These procedures will standardize trial conduct across sites and provide a clear reference in cases of disagreement.

④ All research staff must undergo centralized training, which includes the study’s objectives, protocol requirements, diagnostic and treatment standards, randomization procedures, acupuncture techniques, and the use of evaluation tools. Training duration will vary by role, and investigators assigned to the same role at different centers must pass a consistency assessment before participating. Video records of these assessments will be archived for quality assurance.

⑤ A trial management team will be established, led by the principal investigator. Center-specific monitors will be appointed to oversee trial conduct and ensure quality control at each site.

⑥ A unified, preprinted case report form (CRF) will be used across all sites. Each CRF will be numbered and its assignment recorded. Investigators must complete CRFs objectively, accurately, and in accordance with the trial protocol. Any issues or deviations encountered during the study must be truthfully recorded.

⑦ To maintain the integrity of the blinding process, principal investigators and data analysts will remain blinded to group assignments. Study functions—including participant recruitment, treatment administration, data collection, entry, and statistical analysis—will be performed independently by different personnel.

⑧ Patient compliance will be promoted through comprehensive education on the study’s purpose and significance. Written informed consent will be obtained from all participants. Acupuncture treatment costs will be fully covered by the study’s funding.

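### Section 2.7 records adverse reactions in the 8 treatment weeks only: it states no recording of SAEs or all-cause events, and plans no safety assessment in weeks 9–24

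*Protocol*

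**What the plan says.** Section 2.7 of the protocol contains the only sentence that sets up safety recording: "Any adverse reactions occurring during acupuncture treatment will be documented". The list of reaction types is open-ended. The section closes with "Assessment time point: Throughout the treatment period". The rest of it covers how events are managed and who bears the cost.

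Section 2.4 (text after Table 2) fixes the length of treatment: "for a total of 20 sessions over an 8-week treatment period".

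Section 2.5 follows efficacy well past that point: "Changes in LARS Score from Baseline at Week 2, 4, 6, 12 and 24". The distress rating, both quality-of-life questionnaires, the stool diary and the Wexner score are also collected at weeks 12 and 24.

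Section 2.1.6 lists among its grounds for withdrawal "The occurrence of serious adverse events (SAEs), severe complications, or the need for reoperation", where the investigator judges that staying in the trial would not serve the patient.

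Two other passages create general recording duties. For withdrawals, section 2.1.5 asks investigators to "document the reasons for withdrawal, and complete as many assessments as possible". On the CRF, section 2.10 says "Any issues or deviations encountered during the study must be truthfully recorded".

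**The concern.** What is collected, and when, is fixed by the protocol; an analysis plan cannot recover events that nobody asked about. Section 2.7 fixes both narrowly. It documents reactions, a term that normally implies a link to the intervention, and it stops when treatment stops. Yet the protocol treats SAEs and reoperation as important enough to act on, and it keeps participants under assessment for four months after the last session.

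At stake is the safety statement at the end of the trial. If events are written down only when seen as reactions to acupuncture, or only when they lead to withdrawal, the counts by arm will not be complete or comparable, and nothing systematic can be said about weeks 9–24.

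**Working it through.** The point turns on comparing passages; the arithmetic is small.

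**1. Length of the safety window.** Section 2.4 gives three sessions a week for four weeks and two a week for four weeks: 3 × 4 + 2 × 4 = 20 sessions over 4 + 4 = 8 weeks. This reproduces the protocol's own total. The window in section 2.7 is therefore weeks 1–8.

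**2. Length of follow-up.** The last assessment in section 2.5 is at week 24. Weeks without planned safety assessment: 24 − 8 = 16. Share of follow-up: 16/24 = 67%. Two scheduled assessments, at weeks 12 and 24, fall in that stretch.

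**3. What is recorded compared with what is acted on.**

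| Section | Kind of event | What the protocol does |
| --- | --- | --- |
| 2.7, opening sentence | Adverse reactions | Documents them |
| 2.7, later text | All adverse events | Manages them |
| 2.7, cost clause | Events related to the intervention | Assigns costs |
| 2.1.6, item 1 | SAEs, severe complications, reoperation | Withdraws, if the investigator so judges |

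The cost clause speaks of events related to the intervention, so the protocol itself recognises a wider class than related events. The recording duty is attached only to reactions. Section 2.7 does not mention SAEs and gives no step for recording or reporting them.

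**4. Do the general recording duties fill the gap?**
- *Withdrawal reasons (section 2.1.5).* Item 1 of section 2.1.6 is conditional on the investigator's judgement. A participant who has an SAE and stays in the trial leaves no withdrawal reason. After week 8 there is no treatment left to stop, so an event is less likely to lead to withdrawal at all.
- *CRF issues (section 2.10).* This has no week-8 limit, so a later event could be entered. But it prompts no question about events, sets no definition, and does not ensure that both arms are asked alike.

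Both can leave a record of some events. Neither gives a count by arm that can be relied on.

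**5. What does not change.** No sample-size or efficacy figure depends on this point.

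**The case against.** The strongest reply is that the protocol does not shut these events out. The list in section 2.7 is open. The timing in "Any adverse reactions occurring during acupuncture treatment will be documented" most naturally means the whole course: the section also deals with soreness after a session, and its stated time point is the treatment period. The investigator must learn of an SAE or reoperation to apply section 2.1.6, and sections 2.1.5 and 2.10 would leave some trace. Sections 2.1.6 and 2.7 can also both be followed as written, since one is a withdrawal rule and the other a recording rule. All 20 sessions fall inside the safety window. The operating procedures and the CRF, which might say more, are not at hand.

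Most of this stands, and it rules out three stronger readings.

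- A reader might infer that only reactions within a session count, or that SAEs, reoperations and every event after week 8 are lost. The text does not go that far. What is missing is structured capture.
- A reader might infer that the acupuncturist, the one unblinded role in section 2.3, decides what counts as a reaction and so biases the comparison. No passage says so. Section 2.7 names the acupuncturist only when an event has to be managed or referred, and section 2.10 gives treatment and data collection to different personnel.
- A reader might add an upper confidence bound on the event rate when none is seen. That bound reflects the number of participants and would be the same with perfect collection to week 24, so it does not measure this defect.

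What the reply does not remove is the stated window ending at week 8 and the absence of any stated recording of SAEs or all-cause events.

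**Conclusion.** The point holds in a limited form. Following section 2.7 as written gives recording of adverse reactions in weeks 1–8, no stated recording of SAEs or all-cause events, and no planned safety assessment in 16 of 24 follow-up weeks (67%). Scattered records through withdrawals or CRF issues would not support a balanced safety statement by arm through week 24.

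The 67% describes calendar time only. The documents give no rate for late events, so the number of events that would be missed cannot be estimated, and a large loss should not be inferred. The conclusion assumes that the treatment period in section 2.7 is the 8 weeks of section 2.4, and that no operating procedure or CRF page outside the protocol already widens collection. The primary outcome at week 8 is untouched. This is a worthwhile, low-cost improvement, not a threat to the trial's main result.

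**What to change.** Amend section 2.7 as follows:

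- Record all adverse events and SAEs regardless of judged cause, in both arms, from the first session to week 24.
- Ask one standard, cause-neutral question at the assessments that already exist, including weeks 12 and 24. Ask it after the efficacy scales, so that an answer hinting at allocation cannot colour them.
- Record the causality judgement as a separate item, and report events by arm.
- Reconcile section 2.7 with section 2.1.6, so that every event on which the withdrawal rule can act is also recorded as safety data. The withdrawal rule itself need not change for this purpose.

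The cost is an amendment, an added CRF item, somewhat more event reporting (including separate causality entries up to week 24), and a small risk that a participant's answer unblinds the assessor. Asking the question last limits that risk at each assessment but does not remove it for later ones.

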**2.8 Data Entry and Statistical Analysis**

A modified intention-to-treat (mITT) approach will be applied. All randomized participants who meet inclusion criteria will be included in the statistical analysis. Continuous variables will be expressed as mean ± standard deviation (M ± SD) or as median with interquartile range, depending on distribution. Categorical variables will be presented as frequencies, proportions, or percentages.

Baseline demographic and clinical characteristics will be compared using analysis of variance (ANOVA) or chi-square (χ²) tests. Between-group differences in outcomes will be analyzed using t-tests, rank-sum tests, ANOVA, or χ² tests, as appropriate. For repeated measures outcomes, repeated-measures ANOVA will be employed.

All statistical tests will be two-sided, with a significance level of α = 0.05. A p-value < 0.05 will be considered statistically significant. Statistical analyses will be conducted using SPSS software.

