**2.2 Sample size**

Based on previous study, we speculated that the LARS score would be decreased by 6.8 points in the electroacupuncture group and 4.1 points in the sham-electroacupuncture group, with a standard deviation of 5. Considering a 20% dropout rate, it is estimated that a total of 136 subjects will need to be recruited.

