**2.5 Outcome Measures**

**Primary outcome**

Change in LARS score from baseline at week 8.

The LARS score is a validated self-rating scale to assess bowel function after low rectal resection and consists of five items: fecal incontinence, urinary incontinence, bowel frequency, bowel aggregation, and urgency, with scores ranging from 0 to 42. The severity of bowel dysfunction can be categorized as: no LARS (0-20), mild LARS (21-29), or severe LARS (30-42).

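### No single primary test is named for the week-8 LARS change, and none of the listed tests adjusts for baseline LARS or centre: valid, but it gives up precision that costs nothing to collect

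*Protocol*

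**What the plan says.** Section 2.5 of the protocol defines the primary outcome as "Change in LARS score from baseline at week 8", and section 2.6 repeats the change from baseline as the main efficacy measure. LARS change is also a secondary outcome at weeks 2, 4, 6, 12 and 24.

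Section 2.8 holds all of the analysis text: "Between-group differences in outcomes will be analyzed using t-tests, rank-sum tests, ANOVA" or chi-square tests, whichever is judged suitable. One further sentence gives repeated-measures ANOVA for repeatedly measured outcomes. No method is tied to the primary outcome and no covariate is named.

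Section 2.3 stratifies the 1:1 randomisation by study centre only. Section 2.1.3 admits anyone with a LARS score of 21 or more, so baseline can lie anywhere from 21 to 42.

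Section 2.2 gives the planning assumption: "the LARS score would be decreased by 6.8 points in the electroacupuncture group and 4.1 points in the sham-electroacupuncture group". The SD is taken as 5 points. After an allowance of 20% for dropout, the section concludes: "it is estimated that a total of 136 subjects will need to be recruited". Section 2.8 sets the error rate: "All statistical tests will be two-sided, with a significance level of α = 0.05".

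**The concern.** There are two linked weaknesses.

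**The primary result is not tied to one method.** LARS is continuous and is measured at six post-baseline visits. A t-test, a rank-sum test, ANOVA (the same as the t-test with two groups) or repeated-measures ANOVA could each be presented as the primary analysis under section 2.8. They do not answer the same question. The trial is sized on a mean difference at week 8. The rank-sum test does not estimate a mean difference. Repeated-measures ANOVA over all visits tests overall group and time effects unless a week-8 contrast is specified.

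**The named methods leave baseline information unused.** A change score uses baseline only by subtraction, which fixes the slope of week 8 on baseline at 1. If the true slope is lower, regression adjustment gives a smaller standard error and removes the part of the estimate that comes from a chance difference in baseline LARS between the arms. Nothing in the design balances baseline severity, because centre is the only stratifier. Centre itself is built into the randomisation but not into the analysis.

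At stake are the precision of the primary estimate and a clear link between the analysis and the sample size.

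**Working it through.** **Inputs from the protocol.** Mean falls of 6.8 and 4.1, so a difference of 2.7; SD 5, read as the SD of the change; 20% dropout; total 136; two-sided alpha 0.05; 1:1 allocation. Power is not stated; 80% is an assumption that reproduces the total.

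**Step 1: the protocol's own figure.** n per arm = 2 × (1.96 + 0.8416)² × 5² / 2.7² = 53.8, rounded up to 54. Dividing by 0.8 gives 67.5, rounded up to 68 per arm, or 136 in total. The stated size reproduces and corresponds to an unadjusted two-sample comparison. Power with 54 completers per arm is 80.1% by the normal approximation and 79.4% by the t-distribution. The t-based figure is used below.

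**Step 2: effect of adjusting for baseline.** Let the week-8 SD be k times the baseline SD, with correlation ρ between them. Neither is in the protocol. Up to a common factor:

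- variance of the change score: 1 + k² − 2kρ
- residual variance after ANCOVA: k²(1 − ρ²)
- variance ratio R = k²(1 − ρ²) / (1 + k² − 2kρ), which is (1 + ρ)/2 when k = 1

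Holding the change SD at 5, the adjusted SD is 5√R. Example for k = 1, ρ = 0.5: R = 0.75, adjusted SD 4.33, SE lower by 13%. Example for k = 1.25, ρ = 0.3: R = 1.5625 × 0.91 / (2.5625 − 0.75) = 0.784, adjusted SD 4.43, SE lower by 11%.

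| k (assumed) | ρ (assumed) | R | SE reduction | Power, 54 per arm |
|---|---|---|---|---|
| no adjustment | – | 1 | – | 79.4% |
| 1 | 0.3 | 0.650 | 19% | 93.2% |
| 1 | 0.5 | 0.750 | 13% | 89.4% |
| 1 | 0.7 | 0.850 | 8% | 85.4% |
| 1.25 | 0.3 | 0.784 | 11% | 88% |
| 1.25 | 0.5 | 0.893 | 5.5% | 84% |
| 1.25 | 0.7 | 0.981 | 1% | 80% |
| 1.5 | 0.3 | 0.871 | 6.7% | 85% |
| 1.5 | 0.5 | 0.964 | 1.8% | 81% |
| 1.5 | 0.7 | 0.998 | 0.1% | 79.5% |

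The few degrees of freedom spent on covariates are ignored. No gain is credited to centre, since the number of centres and the variation between them are not given.

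The rows with k above 1 matter because entry cuts baseline off below 21, while the week-8 score can fall anywhere on the 0–42 scale. Baseline spread may therefore be the narrower of the two.

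**Step 3: sensitivity to chance imbalance.** With k = 1, the baseline SD is 5/√(2(1 − ρ)). A baseline difference of one standard error moves the change-score estimate by (1 − ρ) × baseline SD × √(2/54). That is 0.57, 0.48 and 0.37 points for ρ = 0.3, 0.5 and 0.7, or 21%, 18% and 14% of 2.7. This is scatter that the unadjusted standard error already contains; ANCOVA removes it.

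**Step 4: cost of choosing between tests.** In a null simulation (20,000 runs, normal data, 54 per arm, ρ = 0.5), the t-test on change had a type I error of 5.1%. Taking the smaller p-value of the t-test and rank-sum test gave 5.9%. Repeated-measures ANOVA was not simulated.

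**The case against.** **The unadjusted test is valid.** Under 1:1 randomisation the difference in mean change is unbiased, and its standard error already allows for chance imbalance. A reader might infer that chance imbalance, or regression to the mean from the entry cut-off, biases the treatment effect. The protocol does not support that: the cut-off acts on both arms alike. What is lost is precision, and protection given the imbalance that actually occurs. This objection stands.

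**The gain may be small.** The favourable figures need equal SDs at baseline and week 8, which the entry rule makes doubtful. With a wider week-8 spread and a high correlation, almost nothing is gained. This also stands, so the gain must be quoted as a range.

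**Choice after seeing the data is an inference.** Section 2.8 does not say when the test is chosen. Its remark about distribution concerns descriptive summaries. Sections 2.3 and 2.10 keep analysts blinded, and the inflation from choosing between t-test and rank-sum is modest. A reader might infer that the p-value is open to manipulation; the text does not go that far. Blinding still does not say which test is primary.

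**The detail may be in an unseen SAP.** Covariates are often settled there, and section 2.8 does not forbid them. But the protocol has gone further than silence: it lists its methods, and none is adjusted. Naming a better one improves what the protocol states.

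**Category improvement.** The endpoint counting "the number of patients improving from severe LARS to mild LARS, from mild LARS to no LARS" also depends on baseline: a score of 31 needs a 2-point fall to reach 29, a score of 41 needs 12. That comes from the endpoint's definition. A crude chi-square test is valid there, and logistic adjustment would target a different, conditional odds ratio.

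**Conclusion.** The point holds as a low-cost improvement, not as a fault in validity. Section 2.8 ties no single method to the primary outcome, and every method it lists omits baseline LARS and centre as covariates. Two of the options, rank-sum and repeated-measures ANOVA without a week-8 contrast, do not target the 2.7-point difference behind the sample size.

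The size of the gain is uncertain. From 79% unadjusted, power rises to about 85–93% with equal SDs and a correlation of 0.7 to 0.3, and to about 79–88% when the week-8 SD is 1.25 to 1.5 times the baseline SD. Both quantities are assumptions, as is reading the SD of 5 as that of the change. Since 136 reproduces from the protocol's inputs at an assumed 80% power, a reader should not infer that the trial is underpowered on its own figures.

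**What to change.** In section 2.8, name one primary analysis: ANCOVA of the week-8 LARS change with treatment, baseline LARS and centre as terms, reported as an adjusted mean difference with 95% CI whatever the observed distribution. Keep the rank-sum test as a sensitivity analysis only, and repeated-measures ANOVA for secondary description of the time course. Baseline-adjusted analysis of category improvement is optional.

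The cost is one or two sentences. Baseline LARS is needed for the change score in any case and centre is known from randomisation, so no new data, visits or participants are required. The sample size can stay at 136, with any gain in precision kept as a margin.

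### Repeated-measures ANOVA, unless values are imputed, analyses only participants with every visit, which conflicts with the stated mITT set; section 2.8 also leaves open whether it tests week-8 LARS change

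*Protocol*

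**What the plan says.** The primary outcome in Protocol section 2.5 is a single-time-point measure: "Change in LARS score from baseline at week 8". The first secondary outcome adds five more LARS assessments: "Changes in LARS Score from Baseline at Week 2, 4, 6, 12 and 24". LARS is therefore scored at six post-baseline visits. The distress rating, EORTC-QLQ-C30, FIQL and Wexner score are also repeated, at weeks 4, 8, 12 and 24.

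Section 2.8 defines the analysis set under a modified intention-to-treat heading: "All randomized participants who meet inclusion criteria will be included in the statistical analysis". It then gives two sentences on methods. The first is a menu: "Between-group differences in outcomes will be analyzed using t-tests, rank-sum tests, ANOVA, or χ² tests, as appropriate". The second is specific: "For repeated measures outcomes, repeated-measures ANOVA will be employed". Neither names an outcome, and no test is assigned to week-8 LARS change. Section 2.6 describes the primary efficacy indicator as LARS change from baseline without giving a week.

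On missing participants, section 2.2 plans for loss ("Considering a 20% dropout rate"). Section 2.1.5 says that those who withdraw are not replaced and that their records are kept "for inclusion in full analysis set (FAS) statistical processing".

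**The concern.** Classical repeated-measures ANOVA needs a value at every visit in the model. Unless missing values are filled in first, a participant who misses one visit contributes nothing, even to visits that were attended. Someone with a week-8 LARS score who misses week 24 is removed. The protocol expects a fifth of participants to drop out and undertakes to analyse them all, so the named method, used as written, does not deliver the named population.

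Three things are at stake:

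- **Selection.** If people who do not improve are more likely to leave, the analysed group is a selected one, and the comparison is no longer protected by randomisation.
- **Discarded data.** Week-8 scores that were collected may not be used.
- **The question answered.** The default outputs are a group main effect, which averages over visits, and a group-by-time interaction. Neither is the week-8 difference that section 2.5 makes primary.

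**Working it through.** **Inputs from the protocol.** Expected LARS scores "decreased by 6.8 points in the electroacupuncture group and 4.1 points in the sham-electroacupuncture group", a difference of 6.8 − 4.1 = 2.7; SD 5; 20% dropout; total 136 (section 2.2). Allocation 1:1 (section 2.3). Two-sided α = 0.05 (section 2.8). Six post-baseline LARS visits (section 2.5). Power is not stated.

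**Step 1: reproduce the sample size.** Per arm, n = 2 × (1.96 + 0.8416)² × 5² / 2.7² = 53.8, so 54. Inflating for dropout, 54 / 0.80 = 67.5, so 68 per arm and 136 in total. This matches at 80% power. The same method gives 156 at 85% and 184 at 90%, so 80% is the inferred target. The calculation is a two-sample comparison of mean change at one time point, with 108 evaluable.

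**Step 2: complete cases and power.** The protocol gives no visit-level missingness, so I assume a range: each of six visits is missed independently with probability m, on top of 20% dropout by week 24.

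- Complete cases = 136 × 0.80 × (1 − m)⁶
- Power = Φ(0.54 × √(N/4) − 1.96), where 0.54 = 2.7/5 and N is the total analysed (normal approximation)

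For comparison, the last two columns use everyone with a week-8 value. If the 20% dropout is spread evenly over 24 weeks, the fraction still in the trial at week 8 is 1 − 0.20 × 8/24 = 0.933, and N = 136 × 0.933 × (1 − m).

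| m per visit (assumed) | Complete cases | Power | With a week-8 value | Power |
|---|---|---|---|---|
| 0% | 108.8 | 0.80 | 126.9 | 0.86 |
| 2% | 96.4 | 0.76 | 124.4 | 0.85 |
| 5% | 80.0 | 0.68 | 120.6 | 0.84 |
| 10% | 57.8 | 0.54 | 114.2 | 0.82 |

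In the first row about 127 − 109 = 18 people with an observed week-8 score would be discarded. That number depends on when people leave. If all dropout fell before week 8, about 109 would have a week-8 value, and at m = 0 the two approaches would use the same people.

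**Step 3: main effect against week-8 effect.** The main effect averages the visit-specific differences. Take a true week-8 difference of 2.7 and three assumed profiles over weeks 2, 4, 6, 8, 12 and 24:

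- Constant: 2.7 × 6/6 = 2.70, no dilution.
- Rising 25%, 50%, 75%, 100%, then held: 2.7 × 4.5/6 = 2.03.
- The same rise, then waning to 75% and 50%: 2.7 × 3.75/6 = 1.69.

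The protocol gives no time profile, so this is a range and not an estimate.

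**The case against.** The strongest reply is that the protocol never assigns repeated-measures ANOVA to the primary outcome. Week-8 change is one value per person, the preceding sentence of section 2.8 allows a t-test or ANOVA, and Step 1 shows that the sample size is exactly that comparison. This stands. A reader might infer that the primary analysis is a repeated-measures ANOVA and that the week-8 effect will not be estimated. The text does not support that. It leaves the choice open, and a week-8 contrast can in any case be taken from a repeated-measures model.

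Second, deletion follows only if nothing is imputed. A missing-data rule may sit in a statistical analysis plan that is not shown, so its absence is no finding. Section 2.1.5 asks for as many assessments as possible after withdrawal, and section 2.1.6 counts some withdrawals as failures, so the intent to retain dropouts is clear. This stands in part: the protocol commits to a method that, as written, works against that intent.

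Third, a reader might infer that the trial loses power on its own figures. It does not. At the stated 20% dropout, about 109 complete cases meet the 108 planned. The lower figures need intermittent misses, which are assumed.

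Fourth, a single diluted effect or a single bias percentage is tempting to quote. Dilution depends on an assumed profile, and bias on an assumed dropout rule. The documents fix neither.

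**Conclusion.** The concern holds in a conditional form. Section 2.8 names a method for repeated outcomes that, without imputation, is a complete-case analysis. That is at odds with the section's own mITT statement and with section 2.1.5. It reaches the LARS scores over time and the other repeated continuous scales, and because no test is assigned, it could reach the primary outcome as well.

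At the protocol's own dropout rate the cost is a departure from the stated population and a risk of selection bias, with power still at about the inferred 80%. Power falls below that only with intermittent misses: to about 0.76 at an assumed 2% per visit and 0.54 at 10%. The gain from using every week-8 value (about 127 against 109 participants, power 0.86 against 0.80) assumes evenly spread dropout and no intermittent misses. It vanishes if everyone who leaves does so before week 8 and no other visit is missed. Dilution of the main effect runs from none to about 2.0 or lower instead of 2.7, according to the assumed profile.

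**What to change.** In Protocol section 2.8, replace repeated-measures ANOVA with a mixed model for repeated measures, fitted by REML to all available post-baseline scores. Include treatment, visit, treatment-by-visit, baseline score and centre (the stratification factor). State that the week-8 LARS treatment contrast from this model, with its 95% confidence interval, is the single primary result. Use the same model for the other repeated continuous outcomes.

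The cost is two or three sentences, with no new data or participants. The MIXED procedure in SPSS, the software already named, fits the model.

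There is a small downside. The model relies on data being missing at random, and a participant with no post-baseline score contributes no outcome data. The analysis-set sentence should say so, since even this model does not literally include every randomised participant.
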